## Intervention

### Electronic mindfulness-based intervention

The eMBI presented here (*mindmom intervention*) was adapted to pregnancy by an interdisciplinary team of gynecologists, psychologists, and midwives and takes place between the 29th and 36th gestational weeks [35]. The eMBI comprises an established concept of eight weekly 45-min sessions [34] including psychoeducational content, approaches derived from cognitive behavioral therapy and mindfulness exercises especially adapted to pregnancy [36]. *Mindmom* teaches how to deal with stress, pregnancy- and birth-related anxiety, and perinatal depressive symptoms and supports the autonomy of the expectant mother with regard to the upcoming birth and the initial time with the baby. The app contains instructional videos, audio files, interactive worksheets, and a personal skills box in which the participant can collect exercises, texts, and videos that were perceived as helpful. Table 1 gives an overview of the contents of the *mindmom* sessions.

**Table 1 Tab1:** Overview of the *mindmom* program

Module 1	Module 2	Module 3	Module 4	Module 5	Module 6	Module 7	Module 8
**Introduction** (the idea behind skill and mindfulness training)	**Fears and worries about birth/parenting**	**Coping with stress**	**Birth-related pain control**	**Birth**	**Me and my baby**	**Outlook puerperium**	**Graduation module—a review of all modules**

In order to improve adherence to the intervention, participants will be reminded by email about pending appointments and visits. Additionally, elements of gamification were implemented to support user compliance.

### Course of study

The beginning of the study is scheduled for the 29th gestational week. Every study participant receives access to the *mindmom* app. Participants of both groups (IG and TAU) are requested to complete digital assessments, which are scheduled every 2 weeks for the period of the intervention (visits 1–5), as well as 1 and 5 months postpartum (visits 6 and 7). The assessments are completed via the *mindmom* app and contain self-report questionnaires, sociodemographic and medical data, physiological measures, and morning cortisol profiles, which will be sent to the responsible study center by post. Table 2 provides an overview of the visit schedule and its content. Moreover, all study participants have access to an online pregnancy guidebook embedded in the mindmom app that provides valid information about pregnancy and birth on a weekly basis. Women in the TAU group are encouraged to participate in regular antenatal care and are conveyed to mental health care services, if required. The IG participates in the eMBI. Figure 1 shows the flow chart of the mindmom study. Figure 2 shows the schedule of enrolment, interventions, and assessments of the mindmom study.

**Table 2 Tab2:** Study outcomes

	Time of assessment	Study outcomes	Instruments
**T1**	28th gestational week	• Symptoms of depression and (pregnancy-related) anxiety • Maternal-fetal attachment • Quality of life • Mindfulness • Morning cortisol profile • Sociodemographic variables (age, educational level, family status, income, occupation, number of children) • Medical history (gravidity, parity, fertility treatment) • Blood pressure, pulse, height, weight	EPDS, STAI, PRAQ-R MFAS EQ-5D FFA-14
**T2**	30th gestational week	• Symptoms of depression and (pregnancy-related) anxiety • Blood pressure, weight	EPDS STAI, PRAQ-R
**T3**	32nd gestational week	• Symptoms of depression and (pregnancy-related) anxiety • Maternal-fetal attachment • Quality of life • Blood pressure, weight	EPDS STAI, PRAQ-R MFAS EQ-5D
**T4**	34th gestational week	• Symptoms of depression and (pregnancy-related) anxiety • Blood pressure, weight	EPDS STAI, PRAQ-R
**T5**	36th gestational week	• Symptoms of depression and (pregnancy-related) anxiety • Maternal-fetal attachment • Quality of life • Mindfulness • Morning cortisol profile • Blood pressure, weight	EPDS STAI, PRAQ-R MFAS EQ-5D FFA
**T6**	1st month postpartum	• Symptoms of depression and anxiety • Postpartum bonding • Satisfaction with medical care around the birth • Satisfaction birth • Breast feeding behavior • Blood pressure, weight • Medical details on current birth	EPDS, STAI PBQ-16 PEQ-G
**T7**	5th month postpartum	• Symptoms of depression and anxiety • Postpartum bonding • Mindfulness • Blood pressure, weight • Breastfeeding behavior • Morning cortisol profile • Technical handling and acceptance of the *mindmom* app	EPDS, STAI PBQ-16 FFA-14
**T1–7**	Continuously	• Out-of-pocket payments for alternative diagnostic and therapeutic methods, homeopathic products or non-prescription drugs	Cost diary

**Fig. 1 Fig1:**
[figure not shown]
Flow chart of study

**Fig. 2 Fig2:**
[figure not shown]
Schedule of enrolment, interventions, and assessments of the mindmom study

### Primary outcomes

#### The Edinburgh Postnatal Depression Scale

Symptoms of depression during pregnancy are assessed with the German version of the EPDS [37, 38]. The EPDS is a 10-item questionnaire that is used as a screening instrument and for research purposes. Item scores are summed up to a total score, with higher scores indicating a higher symptom burden. At a cutoff value of 9 (EPDS > 9), the sensitivity of detecting a clinically significant depression is 0.96, the specificity is 1.00, and the positive predictive value is 1.00 [37–39]. The scale has a good internal consistency (Cronbach’s α = 0.81).

#### State-Trait Anxiety Questionnaire

Symptoms of anxiety are assessed according to the German version of the State-Trait Anxiety Questionnaire (STAI), a 40-item questionnaire based on Cattell’s model of anxiety (Laux et al. [40]; Spielberger et al. [41]). The STAI consists of 2 subscales separately assessing anxiety as both a general trait and a temporary condition, which may be used together or separately, each showing an excellent internal consistency (Cronbach’s α = .90) [40–42].

#### Pregnancy-Related Anxiety Questionnaire

Pregnancy-related anxiety is measured with the German abridged version of the Pregnancy-Related Anxiety Questionnaire (PRAQ-R) [43–45]. The PRAQ-R consists of 10 items with three subscales (birth anxiety, fear of having a physically or mentally ill child, and worrying about one’s own physical appearance). The internal consistency for global scale is good [44].

### Secondary outcomes

#### Perceived attachment towards the fetus

The attachment to the unborn child is evaluated by using the revised German version of the Maternal-Fetal Attachment Scale (MFAS) [44, 46]. The MFAS is a 24-item questionnaire with 4 subscales (anticipate interaction with the baby, personal involvement, name the baby, and interaction with the fetus). The internal consistency of the questionnaire is acceptable with a Cronbach’s alpha of 0.792.

#### Postpartum Bonding Questionnaire

The quality of postpartum bonding is evaluated by applying the abridged version of the Postpartum Bonding Questionnaire (PBQ-16) [47, 48]. The PBQ-16 consists of 16 items and has a good internal consistency (Cronbach’s α = .85).

#### Quality of life

Health-related quality of life is measured with the EQ-5D-5L, a generic instrument that was developed by the EuroQol Group [49–51]. The internal consistency is good (Cronbach’s alpha of 0.83). Several studies show that EQ-5D is a valid instrument during the peripartum period, too [51].

#### Mindfulness

Individual mindfulness as a personal trait is evaluated by using the abridged version of the “Freiburger Fragebogen zur Achtsamkeit” (FFA-14 questionnaire) [52, 53]. The internal consistency is good (Cronbach’s α = .86).

#### Birth experience

Satisfaction with birth-related medical care (medical care, midwives, nursing staff, and service) is assessed with the Patients’ Experience Questionnaire Birth (PEQ-G). The PEQ-G consists of 18 items and has an excellent internal consistency (Cronbach’s α = 0.9102) [54].

#### Cortisol profile

Cortisol awakening response is measured by saliva samples (*Awakening Response*) in order to assess individual stress levels objectively [55].

#### Measures for cost-effectiveness

Health care service use and costs for both groups will be measured by means of secondary claims data of the statutory health insurers. This includes direct costs such as general and specialist care, medication, hospitalization, therapeutic products, medical aids, and other services related to pregnancy as well as costs associated with absenteeism. Further, the out-of-pocket costs by families will be assessed using a specific self-completing cost diary.

### Risk-benefit assessment

We do not expect any major risks associated with study participation for the pregnant woman or the fetus. The radiation exposure due to the use of the app is negligible. A detailed risk assessment is carried out as part of the psychological assessment. If acute suicidal tendency is detected by the EPDS screening during study participation, the responsible coordinating body will be alerted. If the study participant feels emotionally burdened, for example, by attending the regular visits, contact with the coordinating office can be made at any time. The interests of study participants always have priority. If participation in the study causes any kind of psychological stress, participation can be terminated at any time.

### Data collection and management

Data will be collected via (1) the mindmom app based on electronic Patient-Reported Outcomes (ePRO) and (2) entries of the study staff to the electronic case report (baseline anamnesis and physiological data). Participants will receive computer-generated emails or smartphone reminders to complete questionnaires. These reminders will occur at baseline and 2, 4, 6, and 8 weeks. Data storage and transfer are encrypted. Plausibility check is carried out as soon as the data are entered into the system. Data entry is protected by individual access data for each member of the study staff. All participants receive pseudonymized study IDs by the coordinating bodies. The study key is encrypted, is only accessible by the study staff and the developers of the application, and will be deleted after study completion. Information gathered with the mindmom app is regularly and incrementally merged with the information provided by the eCRF at the evaluating institute via the pseudonymized study IDs. For research data analysis, only pseudonymized data will be used meaning that identifying data is separated from medical data. If data is shared, it will only be shared without the participants’ identifier. A transfer of scientific data to third parties (e.g., the “Open Science Framework Repository”; OSF; https://osf.io/) will only contain anonymized data. The collected primary data will be linked to the secondary claims data provided by the statutory health insurers. To ensure data security, patient data will be pseudonymized by means of the predefined study IDs and appropriate systems for data transfer will be used.

### Data analyses

The results will be reported following CONSORT recommendations [29]. All statistical analyses are conducted by using IBM® SPSS® and AMOS® (current version 26.0.0). Sociodemographic and clinical data will be described by means of frequencies and percentages or means and standard deviations. Confirmatory and exploratory research hypotheses will be analyzed using multivariate analysis of variance with repeated measurements, correlation analysis, and chi-square tests (see Table 3).

**Table 3 Tab3:** Analytic procedure

	Statistical test	Number of tests	Test statistic	Relevant effect
**Confirmative hypotheses**				
**1–3**	2 (group) × 7 (measurement)—ANOVA for repeated measures on the factor “measurement”	2	*F*-distribution	Group × measurement interaction effect
**4–6**	2 (group) × 5 (measurement)—ANOVA for repeated measures on the factor “measurement”	1	*F*-distribution	Group × measurement interaction effect

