## Methods

### Study design

The *mindmom* study is a bicentric prospective randomized controlled trial (RCT) with a repeated measures and crossed-lagged panel design. Participants will be equally allocated to one of the two study arms: “8-week eMBI course” (intervention group) or “Treatment as usual (TAU) alone” (control group). Both groups will be compared regarding superiority of an electronic mindfulness-based intervention over TAU. The study is being conducted at the University women’s hospitals of Heidelberg and Tübingen, Germany. Ethics approval has been obtained from both universities.

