#### Objectives

This study aims to examine the clinical effectiveness and cost-effectiveness of an eMBI (*mindmom* app) within a sample of pregnant women during the third trimester of pregnancy who were screened positive for emotional distress.

The following content-related hypotheses will be examined:

Participation in the intervention leads to (a) decrease of symptoms of depression/anxiety or lowers prevalence of peripartum depression, (b) decrease of neuroendocrine stress markers, (c) increase of quality of life, (d) promotion of a more positive perception of the birth experience and attachment to the newborn, and (e) a reduction in the number of cesarean sections.

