### Sample size

Estimation of sample size and power analysis were calculated with G*Power (Version 3.1.9.2) [32, 33]. The estimation was implemented for the confirmatory hypotheses, which aim for interaction between the between- (group) and within-subject factor (time of measurement), i.e., that the symptom burden develops differently in the two study groups over the course of time. The analysis with the lowest power is the two-factorial ANOVA with the outcome “PRAQ” (5 measurements, see Table 3, hypotheses 4–6).

The estimation is based on type 1 error of α = .016, Bonferroni-adjusted for 3 confirmatory analyses, and a power of 1 − β = .90. The statistically significant effect size is based on the results of a pilot study on mindfulness-based prevention in pregnant women with a history of depression [34]. Based on the mean values, standard deviations, and case numbers reported in this study, a final treatment effect of Cohen’s *d* = .34 (intervention group: *M* = 4.90, *SD* = 5.22, *n* = 21; control group: *M* = 6.62, *SD* = 4.94, *n* = 29) is calculated for the outcome “depressive symptoms” (EDPS score). According to Cohen (1988), this can be classified as a small effect size. Thus, the number of cases for the ANOVA design is estimated for small treatment effects (*f* = .10). Thus, *N* = 196 cases are needed to evaluate the eMBI. Assuming a dropout rate of 30%, the number of cases was determined to be *N* = 280 to reach a case number of *N* = 196 (*n* = 140 for each group or per region and *n* = 70 per group and region). With a sample size of *N* = 196, large- (*f* = .40) and medium-sized (*f* = .25) effects can be detected with a power of 1 − β = .99 and .98, respectively. Only small effects (*f* = .10) cannot be ruled out sufficiently with a power of 1 − β = .27 in case of non-significant between-subject effects.

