Moreover, data will be analyzed by multi-level modeling. Hereby, the repeated measures (level 1) will be nested in the patients (level 2). A simulation study shows that only small samples on level 2 (< *n* = 50) lead to biased estimations of the standard errors on level 2 [58]. Expecting invariant results, the exploratory application of these models can increase the assurance regarding the exclusion of small between subject effects.

In accordance with the ICH Guideline E9, the primary analyses are performed according to the intention-to-treat (ITT) principle. Per-protocol (PP) analyses on sensitivity of effects are implemented in an exploratory fashion.

In order to reliably estimate missing values and thus to protect the analyses against response and selection biases, multiple imputations will be used [59]. First of all, missing values will be tested by Little’s Missing-Completely-At-Random test [60]. Following a negative result, *n* = 20 data sets with all variables of the analytic model are estimated. Hereby, value estimations are restricted to scale-specific ranges. Results are then pooled over the *n* = 20 data sets.

In accordance with the methods proposed by the German Institute for Quality and Efficiency in Health Care (IQWiG), the cost-effectiveness analysis will be carried out from the perspective of the statutory health insurance and, if possible, additionally include a societal and/or individual perspective [61]. The incremental cost-effectiveness ratio (ICER) will be calculated dividing the difference in costs by the difference in health benefit of the intervention compared to standard care. Costs are assessed in monetary units, and the benefit is measured by the primary (severity of symptoms) and secondary outcomes (f. e. cesarean sections, health related quality of life). The perspective of the analysis thereby determines the relevant cost components.

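### The confirmatory group × measurement F test has no direction and spends the pre-treatment visit as an outcome level, so alone it cannot show superiority and it wastes baseline information

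*Protocol article*

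**What the plan says.** The Study design section sets the aim: "Both groups will be compared regarding superiority of an electronic mindfulness-based intervention over TAU". Hypothesis (a) under Objectives has a direction: "decrease of symptoms of depression/anxiety or lowers prevalence of peripartum depression".

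The Sample size section words the confirmatory hypothesis without direction, namely "that the symptom burden develops differently in the two study groups over the course of time". Table 3 follows that wording. Two confirmatory tests are a "2 (group) × 7 (measurement)—ANOVA for repeated measures on the factor" of measurement and one is a "2 (group) × 5 (measurement)—ANOVA for repeated measures on the factor" of measurement. All three are referred to the F-distribution, with "Group × measurement interaction effect" as the relevant effect.

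The seven (or five) measurements include T1, which Table 2 places in the "28th gestational week". The intervention starts in week 29.

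The Data analyses text adds four things:
- It describes the analysis as a multivariate analysis of variance with repeated measurements, whereas Table 3 says ANOVA.
- It names Dunn's procedure for post hoc comparisons.
- It names partial η² and ω² as effect sizes.
- It plans a further model, "Moreover, data will be analyzed by multi-level modeling", for exploratory use.

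**The concern.** A superiority claim needs a signed comparison. A 6-df or 4-df interaction F rejects for any departure from parallel courses. If it is significant, the step from *the courses differ* to *eMBI is better* rests on comparisons chosen among up to seven visits, none of which the article names as confirmatory. The named effect sizes carry no sign.

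Entering T1 as an outcome level means that the test works on contrasts among visits, in effect on changes. It does not use T1 to explain variance in the later scores. What is at stake is the interpretation of a positive result and some avoidable loss of power.

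**Working it through.** **1. The plan's own figures.** Inputs from Sample size: f = .10, α = .016, five measurements, two groups, N = 196. The correlation ρ and the nonsphericity factor ε are not given; ρ = .5 and ε = 1 are assumed.
- λ = f²·N·m·ε/(1−ρ) = .01·196·5/.5 = 19.6 on 4 and 776 df gives power .904 (smallest N for .90: 194). 196/.7 = 280.
- The stated between-subject powers .98 and .27 come out as .981 and .269 with ρ = .5, which supports that value. At ρ = .5 the stated N needs ε = 1. With ε = .75 or .50, power at 196 is .81 or .66.
- Pilot effect: (6.62 − 4.90)/5.06 = .34, with 5.06 the pooled SD.

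**2. Direction.** λ is quadratic in the group differences, so reversing every sign leaves it unchanged. Simulated rejection rates for benefit and for equal harm agree (five visits, compound symmetry .5, constant effect: .49 and .49).

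**3. Cost of using T1 as an outcome level.** For a single contrast, Var(baseline-adjusted)/Var(change) = (1−ρ²)/[2(1−ρ)] = (1+ρ)/2, which is .75 at ρ = .5 and .85 at ρ = .7.

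For the whole course, let δ be the vector of group differences (zero at T1), Σ the correlation matrix of the visits and n = 98 per arm:
- Joint baseline-adjusted test of the post-baseline differences: λ = (n/2)·δ′Σ⁻¹δ, on m−1 and N−m−1 df.
- Multivariate interaction test: λ = (n/2)·[δ′Σ⁻¹δ − (1′Σ⁻¹δ)²/(1′Σ⁻¹1)], on m−1 and N−m df.

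The subtracted term is never negative. The adjusted test therefore has at least as large a λ, on the same numerator df and one fewer denominator df.

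Example: five visits, compound symmetry .5, constant d = .34 after T1. Here Σδ² = .4624, (Σδ)² = 1.8496 and n/2 = 49.
- Adjusted: λ = 49·2·(.4624 − 1.8496/6) = 15.1, power .77.
- Interaction: λ = 49·2·(.4624 − 1.8496/5) = 9.06, power .48.

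Power at α = .016, N = 196, d = .34 (correlation structures assumed):

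| Visits | Correlation | Effect | Multivariate interaction | Joint baseline-adjusted |
|---|---|---|---|---|
| 5 | CS .5 | linear to T5 | .36 | .50 |
| 5 | CS .5 | constant | .48 | .77 |
| 5 | AR(1) .7 | linear to T5 | .16 | .30 |
| 5 | AR(1) .7 | constant | .53 | .74 |
| 7 | CS .5 | linear to T5, then kept | .51 | .70 |
| 7 | CS .5 | linear to T5, gone postpartum | .51 | .57 |

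Under CS .5 with five visits the univariate F is close to the multivariate test (.37 linear, .49 constant).

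**4. Size of the F, if univariate and uncorrected.** Under the null, the F is a ratio of eigenvalue-weighted χ² sums. Under AR(1) .7 and .8, ε is .689 and .631 (five visits) or .584 and .510 (seven). Across simulations, actual size was about .032–.037 (five visits) and .042–.049 (seven), against .016. The multivariate test stayed at .015–.017 and the Greenhouse–Geisser F at .014–.019.

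**The case against.** The strongest reply is that much of this is conditional or already covered.

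- **Dunn's comparisons** are signed and control multiplicity, and the article calls them hypothesis-driven. Table 3 numbers confirmatory hypotheses 1–6, whose wording the article does not reproduce, so a direction may be set elsewhere. This stands in part. The procedure is there, but the article labels it post hoc, and the effect it marks as relevant for the confirmatory tests is the unsigned interaction.
- **T1 as an outcome level** is valid in a randomised trial. That stands: the cost is efficiency, not bias.
- **Type I error.** A reader might infer that the true error rate is not .016. The documents do not support this. They never say that the F is uncorrected, the Data analyses text names a multivariate analysis (which needs no sphericity), and a correction may be left to the full plan. What remains is the mismatch with Table 3 and a sample size that matches ε = 1.
- **A T5-only contrast.** A reader might infer that one baseline-adjusted T5 contrast is always the better test. It is not. With a constant effect from T2 and AR(1) .7/.8 (five visits), its power is .51/.57, against .53/.75 for the multivariate interaction. It would also move the postpartum visits out of the confirmatory question.
- **Planned power.** At the planned f = .10 the power is .904, so the planned test does not fail on its own terms. d = .34 corresponds here to an interaction f of only about .06 to .07, which is a separate sizing matter.

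**Conclusion.** The concern holds in this form: a significant confirmatory interaction does not by itself establish superiority, because it has no direction and the article fixes no confirmatory signed contrast. Using T1 as an outcome level discards information that the trial collects anyway. In the five-visit scenarios above, a baseline-adjusted joint test over the same visits gains 14 to 29 percentage points of power (.36 to .50; .48 to .77). Where the effect vanishes postpartum the gain is smaller (.51 to .57).

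That the adjusted test has at least as large a noncentrality follows algebraically. The size of the gain rests on assumed correlations, d = .34 and the shape of the effect. The excess over α = .016 is a risk only if Table 3 is carried out as an uncorrected univariate F.

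**What to change.** Before unblinding, make the multilevel model confirmatory: post-baseline scores as outcome, T1 score as covariate, group × visit and unstructured covariance. For each of the three scales, test the post-baseline group effect at .05/3.

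Claim superiority only when one pre-specified signed eMBI − TAU estimate, with its confidence interval, favours eMBI. The sponsor chooses whether that is the T5 difference or the average over post-baseline visits. The average does better if the effect is constant after T1 (simulated power .83–.97). It does poorly if the effect builds to T5 and is gone postpartum (.17–.27), where T5 has .51–.65.

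If the ANOVA is kept, reconcile Table 3 with the multivariate analysis named in the text, state that the multivariate or Greenhouse–Geisser test decides, and still name the signed estimate.

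The cost is wording, with no new data. The downside is committing in advance to one estimate. Because a claim would need both the joint test and the signed estimate, its power cannot exceed that of the weaker of the two.
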